### **3.2 Physical Performance**

Both performance-based and self-report instruments will be used to measure physical function. These detailed assessments will be carried out every other year, alternating with the cognitive assessment measures. Performance-based measures are very sensitive to change and can detect early decline prior to the onset of disability in activities of daily living (ADL). They have less of a ceiling effect than other measures of function or self-reported function and, as continuous variables provide more power to assess treatment effect. Small differences in performance (0.1 m/sec in gait speed) are related to important subsequent mortality risk, so that prevention of decline would represent an important treatment effect of aspirin. Self report of increased difficulty with an activity identifies early declines in performance measures, and incident mobility disability. Limitations in or inability to perform ADL and mobility tasks reflect the subject's perception of their ability to perform in their own environment, and correlate moderately with performance-based measures, and therefore are considered to be complementary. Self-report instrumental activities of daily living (IADL) disability measures assess ability to carry out functions such as cooking, shopping and taking medication, which are also important for maintenance of independent living.

#### **a) Performance based measures**

Two performance-based measures will be used: grip strength and gait speed for usual

2258 walking. These two measures are each strong independent predictors of mortality and  
2259 disability, and very sensitive to change. Both can be assessed within 10 minutes and in  
2260 both the home or clinic settings.

2261 Hand grip strength will be measured in kilograms using a handheld isometric dynamometer  
2262 (Jaymar; JLW Instruments, Chicago, Illinois). Grip strength of the dominant hand will be  
2263 measured as the best of three trials. In the Women's Health and Aging Study, the mean  
2264 baseline grip strength was 19.7 ( $\pm$  5.9) kg, and declined by 1.4 ( $\pm$  4.3) kg, or 6.8% over 3 yrs  
2265.

2266 Gait speed will be assessed as the time in seconds to walk 3 meters (8 feet) at the  
2267 participant's usual walking pace from a standing start. Time on the faster of two walks will be  
2268 used to define scores. Gait speed will be examined as a continuous variable. A walking  
2269 speed lower than 0.42 m/s is considered to represent severe walking disability. Speeds  
2270 of less than 1.0 m/sec are predictive of mortality and hospitalization and changes of >0.1  
2271 m/sec related to significant perceived decline.

### 2272 **b) Self-report measures (using ADL and IADL Questionnaires)**

2273 *Mobility activities* – walking one block, walking a quarter of a mile (about 2 or 3 blocks ),  
2274 walking one mile, climbing one flight of stairs, walking in the grocery aisle without sitting or  
2275 leaning on the cart, getting in and out of a car.

2276 *Instrumental ADLs* - doing light housework, preparing own meals, managing own money,  
2277 using the telephone, doing errands, taking care of a family member, visiting relatives or  
2278 friends, participating in community activities, taking own medications.

2279 *Upper extremity activities (tertiary)* - lifting heavy groceries or 10 pounds, raising arms  
2280 overhead, lifting heavy objects, gripping with hands.

### 2281 **c) Frailty measures**

2282 These will include a) measures of gait speed and grip strength (as measured in performance  
2283 measures above) to assess weakness, b) a single item question (from the SF-12 below) on  
2284 fatigue/energy level, c) annual clinic assessment of weight to assess weight loss, and d) a  
2285 single item regarding physical activity, adapted from the LIFE study. These few items can be  
2286 combined to create an assessment of frailty using the Fried criteria. This will be assessed  
2287 every other year in conjunction with the performance measures.

## 2288 **3.3 Maintaining quality of life**

2289 Quality of life will be assessed annually using the Short Form 12 (SF-12) item questionnaire,  
2290 which includes physical functioning, mental health, role functioning (physical and emotional),  
2291 health perceptions in the last year, energy level and pain level. This will provide a basic  
2292 assessment of functioning on a more frequent basis than the more detailed physical function  
2293 assessments which, as stated above, will be conducted every other year.

## 2294 **3.4 Hemoglobin**

2295 Measurement of hemoglobin levels will be undertaken at baseline and annually.

## 2296 **3.5 Hospitalization**

2297 Total hospitalizations and hospitalization for reasons other than endpoints will be collected.  
2298 Hospitalization is defined as an official admission that is for a duration greater than 24 hours or a  
2299 minimum of 2 calendar days where exact time of stay is unavailable.

## 2300 **3.6 Urine albumin:creatinine ratio**

2301 Measurement of urinary albumin:creatinine ratio will be undertaken at baseline and at  
2302 designated annual visits. A ratio higher than the normal value for gender (males: 2.5mg/mmol;

2303 females: 3.5mg/mmol) will be reported to the participant's usual treating doctor for follow up.  
2304

## APPENDIX 2. SAMPLE SIZE & POWER CALCULATIONS

For the primary endpoint, a sample size can be calculated that gives the number of primary endpoint events required for ASPREE to have 90% power for their subsequent analysis by a univariate Cox proportional hazards regression model. To estimate the number of participants required to yield these events, assumptions are made for (i) the event rates that will be seen in ASPREE participants and (ii) the duration of participant follow-up during the study. Having obtained a sample size for the primary endpoint we examine the power or effect size that this number of participants gives us for each secondary endpoint. Hence, assumptions are also required for the event rates of secondary endpoints. In general, Australian event rates have been used as a basis for ASPREE participants. This is justified on the grounds that approximately two-thirds of participants will be recruited in Australia and using the lower Australian rates errs on the conservative side for sample size calculations. For example, Australian rates of all-cause mortality, cardiovascular events and cancer are lower than in the U.S. (see Table 2 of the Research Plan). For the primary outcome, population-specific rates are used where there is strong evidence that a minority group is at increased risk.

The study will have a 1:1 aspirin:placebo group allocation ratio.

All power and sample size calculations were performed with a two-sided alpha error rate of 0.05 for a univariate Cox proportional hazards regression analysis of time to first event using the 'stpower cox' command in Stata (Stata Statistical Software, Release 10, StataCorp, College Station, TX, 2007).

Assumptions used for the original sample size and power calculations include:

- Participants will be 50%, 30%, 15%, 5% in age groups 70-74 years, 75-79 years, 80-84 years, 85 years and over, respectively.
- Participants will be 45% male and 55% female.
- Based on experience with ANBP2, the effect of clustering due to recruitment by country and enrolling general physician or clinical research site will be minimal and no explicit adjustment to the number of participants needs to be made. In any case, since randomization is at the individual participant level, treatment effect is a within-cluster comparison and this protects against any concern over loss of power due to clustering.
- Accrual of participants is over approximately a 2 year period with an average of 5 years of follow-up per participant.
- Rates are assumed for participants based on their age at entry to the study. Further, the rates are assumed to stay constant throughout participants' follow-up.

An amendment to the recruitment strategy in the US in 2011 changed the configuration of the expected participant profile. Specifically the split of recruited participants among the four categories Australian, White US, Hispanic, African American was expected to change to 84.2%, 7.9%, 2.63%, 5.26% respectively. The age distribution in the US participants was expected to change to 20%, 47%, 19%, 8%, 6% in the age bands 65-69 years, 70-74 years, 75-79 years, 80-84 years, 85 years and over, respectively.

### PRIMARY OUTCOME

We have designed ASPREE to have 90% power to detect an effect of aspirin as described by a hazard ratio of 0.90 in an intention-to-treat analysis. Aspirin has dual mechanisms of action likely to affect the primary endpoint. Antiprostaglandin effects are postulated to affect atherogenesis and carcinogenesis and acetylation within platelets is likely to affect atherothrombotic and hemorrhagic events. We would propose that the latter mode of action is likely to have a dominant effect on the primary endpoint due to lag time in the former and

vascular events being the major determinant of morbidity (including dementia and mortality in the aged). The Anti-thrombotic Trialists Collaboration has provided us with a meta-analysis of all six primary prevention trials by age categories which shows that the point estimate of the benefit of aspirin over no aspirin treatment on all-cause mortality alone is 0.95 with wide confidence intervals (95% CI: 0.70 – 1.14) in those subjects aged 70 years and over. The point estimate of aspirin's effect on adverse cardiovascular disease events from the same meta-analysis is 13% (95% CI: 0.65 – 1.16). This suggests that a 10% treatment effect for aspirin is plausible. These studies experienced cross-over of participants from one treatment group to the other for reasons which include the development of a non-fatal, non-disabling cardiovascular or cerebrovascular event necessitating aspirin therapy. Similarly, we expect 5% per annum of placebo-group participants to initiate aspirin use or *vice versa*.

The following assumptions have been made for event rates for the primary endpoint of death from any cause or incident dementia or physical disability (the latter two events defined respectively as an assessment of dementia by DSM-IV criteria and loss of any one of 6 Katz ADLs).

i. Dementia annual incidence rates will be 3 per 1000 for the 65-69y age group (US minorities only), 6/1000 (70-74y), 11/1000 (75-79y), 20/1000 (80-84y), 37/1000 (85y+) for Australian, U.S. Hispanic and U.S. White (non-Hispanic) participants. For U.S. African American the rates are doubled.

ii. Loss of a Katz ADL; annual incidence rate for males = 19.6/1000, females = 26.5/1000 (these incidence rates are from the rates observed in the subset of ASPREE-like participants in the CHS ([name] personal communication, August, 2008) which showed similar rates in U.S. Whites and U.S. minorities). To allow for 20% of the US minority participants being in the 65-69y age group the rates for this population are weighted away from the above rates and towards rates of 13.3 in males and 14.8 in females for this age group. This results in an expected rate of US minorities in the placebo group of 21.5 per 1000 person-years.

iii. Age specific annual mortality rates are from the 2004 Australian population census (source=ICD10 ALL, Australia, 1907–2004 - General Record of Incidence of Mortality, GRIM; <http://www.aihw.gov.au/mortality/data>) apply for the Australian and U.S. White (non-Hispanic) participants. For males these were 2666.1/100000 for the 70-74y age group, 4484.1/100000 (75-79y), 7643.3/100000 (80-84y), 15635.9/100000 (85y+), and for females the corresponding rates were 1467.6/100000 (70-74y), 2722.9/100000 (75-79y), 5107.5/100000 (80-84y), 12892.7/100000 (85y+).

iv. Age-specific mortality rates in U.S. African American and Hispanic participants are based on 2005 rates specific to each minority (U.S. CDC statistics, 2005; <http://www.cdc.gov/nchs>). For male African Americans these were 3227.81/100000 for the 65-69y age group, 4542.75/100000 (70-74y), 6393.35/100000 (75-79y), 8997.85/100000 (80-84y), 13809.8/100000 (85y+), and for female African Americans the corresponding rates were 1963.61/100000 (65-69y), 2901.85/100000 (70-74y), 4288.4/100000 (75-79y), 6337.46/100000 (80-84y), 12789.9/100000 (85y+). For male Hispanics these were 2541.17/100000 for the 70-74y age group, 3899.60/100000 (75-79y), 5984.21/100000 (80-84y), 10140.5/100000 (85y+), and for female Hispanics the corresponding rates were 1639.83/100000 (70-74y), 2649.49/100000 (75-79y), 4280.79/100000 (80-84y), 9068.4/100000 (85y+).

v. Participants will be healthy relative to their same-aged population counterparts and that mortality rates will be 50% lower than the general population rates given in the two assumptions immediately above

vi. To allow for the analysis to be time to first event, individual rates for death, ADL deterioration, and dementia can be summed and the sum reduced by 10% to allow for the potential for different events to occur in the same person.

vii. Using the assumptions above, the overall primary endpoint rate in the Australian and U.S. White participants will be 45.4 per 1000 person years, and the event rate in the U.S. minority groups will be 48.9 per 1000 person years.

The study aims for 5 years average follow-up per participant and for the primary endpoint this 'at risk' time for occurrence of a first primary endpoint event will be reduced to an average of 4.25 years per participant. The reasons for this reduction include censoring due to the occurrence of a primary endpoint, loss to follow-up for death (which is expected to be extremely low due to access to mortality statistics through National Death Index records in Australia and U.S), non-completion of dementia screen or diagnosis, and non-completion of ADL's. In total, we assume that 5% of participants per year will have an occurrence of the primary endpoint or have insufficient follow-up to enable assessment of their primary endpoint status.

On the basis of these assumptions, 311 primary endpoint events in 1500 mainly U.S. minority participants and 3374 primary endpoint events in 17,500 Australian and U.S. White participants will yield 89% power (two-sided alpha error rate of 0.05) to detect a 10% reduction (risk ratio of 0.90) in the primary endpoint with aspirin. The final recruitment numbers that were achieved are approximately 16,500 participants in Australia and 2,500 participants in the U.S. Note that this is a variation from the original protocol which specified a plan to recruit 12,500 and 6,500 participants (4,500 from minority populations all aged 70+y) in Australia and the US respectively which had a 90% power.

**The sample size for the primary endpoint of death from any cause or incident dementia or physical disability will be 19,000 participants.**

## **SECONDARY OUTCOMES**

### ***1. All-cause mortality***

Anticipated rates of all-cause mortality are given above under the primary endpoint sample size calculation. A sample size of 19,000 provides 90% power to detect a hazard ratio of 0.842 comparing the aspirin group with placebo in an intention-to-treat analysis (all other assumptions as for primary endpoint).

### ***2. Fatal and non-fatal cardiovascular events including a) coronary heart disease death, b) non-fatal myocardial infarction, c) fatal and non-fatal stroke and d) hospitalization for heart failure***

- Based on the experience in other primary prevention trials in the elderly it is assumed that the rate of CVD events, (including hemorrhagic stroke; see below) will be 17.0 per 1000 person-years (70-74y age group), 25.0 per 1000 person-years (75-79y), 38.0 per 1000 person-years (80y+).
- These event rates lead to an overall annual rate of 23.6/1000 from which an annual rate of 1.2/1000 for hemorrhagic stroke is subtracted. Hence we expect this secondary endpoint to have an annual rate of 22.4/1000 in the placebo group.
- Assume that there will be an annual loss to follow-up of 3% of participants per annum for this endpoint due to other causes of mortality and, based on ANBP2, an expected very

low rate of non-assessment of non-fatal CVD status. This corresponds to an average of 4.7 years per participant at-risk time. A sample size of 19,000 participants gives 90% power to detect a 14.2% reduction in CVD event risk (hazard ratio 0.858) in an intention-to-treat analysis based on the above assumptions.

### **3. Fatal and non-fatal cancer, excluding non-melanoma skin cancer**

For a sample size of 19,000 subjects to 3% per annum drop out, the study will have 90% power to detect the following hazard ratios for the comparison of incidence rates between intervention and placebo in an intention to treat analysis (assuming rates in the placebo group as described in the table, and other assumptions as for primary endpoint);

|                   | Rates with placebo                         | Hazard ratio |
|-------------------|--------------------------------------------|--------------|
| Colorectal cancer | 3.09 per 1000 person years   | 0.64         |
| Prostate cancer   | 3.04 per 1000 person years   | 0.64         |
| Lung cancer       | 2.52 per 1000 person years   | 0.61         |
| Breast cancer     | 1.95 per 1000 person years   | 0.57         |
| Melanoma          | 1.47 per 1000 person years   | 0.55         |
| All cancer        | 21.35 per 1000 person years  | 0.86         |

The major cancer endpoint will be the incidence (and mortality) of 'All cancers'. The effect of aspirin on colorectal, prostate, lung and breast cancer, and melanoma will be assessed individually as they are the most common cancer types in the population. It is anticipated that with further follow up above and beyond the 5 years currently planned for ASPREE, there would be sufficient power to detect more subtle aspirin effects.

The 'lethality' of cancers occurring in ASPREE will also be addressed. Cancer recurrence, in particular the development of metastatic disease, will be collected in order to see if aspirin may influence the metastatic potential of incident cancers.

### **4. Dementia**

Anticipated rates of dementia are given above under the primary endpoint sample size calculation. A sample size of 19,000 provides 90% power to detect a hazard ratio of 0.807 comparing the aspirin group with placebo in an intention-to-treat analysis (all other assumptions as for primary endpoint).

### **5. Mild cognitive impairment**

Our primary interest is the difference between placebo and aspirin groups in average 3MS rate-of-change from baseline to the end of 5 years of follow-up. Because this measurement is on a continuum, only 5200 participants are required to provide 90% power to detect a clinically relevant 1 point smaller decline over 5 years in the mean 3MS score of the aspirin group than the placebo group. Even assuming the worst-case scenario, for variability in 3MS measurements (for example SD=10) and the strength of correlation between baseline and end-of-study measurements, the sample size of 19,000 participants will be more than sufficient to have 90% power to detect a 1-point smaller decline in this secondary endpoint.

### **6. Physical disability**

Anticipated rates of deterioration in physical ability to perform each Katz ADL are given above

under the primary endpoint sample size calculation. A sample size of 19,000 provides 90% power to detect a hazard ratio of 0.857 comparing the aspirin group with placebo in an intention-to-treat analysis (all other assumptions as for primary endpoint).

## **7. Depression**

We anticipate incidence of new depression of 5% per year based on the estimated probability of healthy older males aged 65-75 years developing major depression in one year. This estimate is globally conservative due to i) evidence that females develop depression at higher rates than males  (the ASPREE population is likely to be 45% male) ii) those aged over 75 have increased probability of depression , iii) incidence of major depression (CES-D >10 points) is lower than pre-morbid depression (CES-D score cut off of 8 points), and iv) the ASPREE study will average 4.25 years of follow up with points (ii-iii) increasing with time. With a sample size of 19,000 followed for an average of 4.25 years with a 3% per annum drop out due to deaths and other primary events, ASPREE has 90% power to detect a hazard ratio of 0.799 comparing the aspirin group with placebo.

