## 2176 **2.7 Depression**

2177 A modified 10 questions version of the CES-D will be used. The modification omits questions  
2178 related to lifestyle that are covered by the LIFE questionnaire. A score of 8 or higher on the 30  
2179 point CES-D 10 questions version is deemed clinically significant and a secondary endpoint  
2180 will have been reached.

2181 Any such score will be communicated back to the family physician, and would typically result in a  
2182 clinical assessment.

2183 Anyone discharged from hospital with a principal diagnosis of depression will be deemed also to  
2184 have reached a secondary endpoint for depression.

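### The detectable hazard ratio for depression (0.799) does not follow from its own inputs, which give about 0.89 to 0.90

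*Protocol*

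**What the plan says.** Appendix 2, Secondary Outcomes, item 7 (Depression) gives the rate: "We anticipate incidence of new depression of 5% per year". It then gives the exposure, "With a sample size of 19,000 followed for an average of 4.25 years", and the losses, "with a 3% per annum drop out due to deaths and other primary events". It concludes that "ASPREE has 90% power to detect a hazard ratio of 0.799 comparing the aspirin group with placebo".

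The opening of Appendix 2 sets the method for every endpoint: "All power and sample size calculations were performed with a two-sided alpha error rate of 0.05". The model named there is a Cox regression of time to first event, run in Stata. On allocation it says: "The study will have a 1:1 aspirin:placebo group allocation ratio".

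The endpoint itself is defined in Appendix 1, section 2.7. The threshold is "A score of 8 or higher on the 30" point CES-D-10, and reaching it is a secondary endpoint. A hospital discharge with depression as the principal diagnosis also counts. The rule does not mention the baseline score.

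**The concern.** A rate of 5% per year over more than four years in 19,000 people should give several thousand events, yet the stated effect is one that fewer than a thousand events could detect.

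The figure also sits badly beside its neighbours in Appendix 2. Disability, at less than half the event rate, has a detectable hazard ratio of 0.857. Dementia, at less than a quarter of the rate, has 0.807. With the same sample size, the most frequent of these three endpoints cannot need the largest effect.

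At stake is the correctness of a published design figure. It presents depression as able to show only a reduction of about 20%, when the stated assumptions support about 10 to 11%.

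**Working it through.** **Inputs.** From Appendix 2, item 7: N = 19,000 (9,500 per arm), placebo rate 0.05 per year, 4.25 years, drop-out 0.03 per year, power 90%. From the opening of Appendix 2: two-sided alpha 0.05, 1:1, Cox model.

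**Formula.** Schoenfeld's events formula for 1:1 allocation: events = 4 × (1.960 + 1.282)² / (ln HR)² = 42.03 / (ln HR)².

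**Does the method match the protocol's other figures?** Yes, exactly or closely.
- Primary endpoint: 42.03 / (ln 0.90)² gives 3,787 events, as stated in section 10.
- Disability: rate 0.45 × 19.6 + 0.55 × 26.5 = 23.4 per 1,000. Over 4.25 years this gives 0.857 (stated 0.857).
- Cardiovascular events: 0.860 (stated 0.858). All cancer: 0.857 (0.86). Major bleeding: 1.229 (1.23).
- Mortality: 0.840 to 0.847 (0.842). Dementia: 0.796 to 0.806 (0.807). Both ranges are for 4.25 to 4.7 years at risk.

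**Events needed for the printed figure.** 42.03 / (ln 0.799)² = 42.03 / 0.05035 = 835 events, and 835 / 19,000 = 4.4%.

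**Events the inputs give.** Solve for the hazard ratio at which expected events equal required events.
1. Rate times person-years, with 4.25 years taken as time at risk net of losses: 19,000 × 4.25 = 80,750 person-years. Events = 80,750 × 0.05 × (1 + HR)/2. The solution is HR = 0.901 with 3,837 events.
2. First event over 4.25 years, no further drop-out: 1 − exp(−rate × 4.25) in each arm. HR = 0.896 with 3,465 events.
3. First event with 3% per year drop-out as a competing loss: probability = r/(r + 0.03) × [1 − exp(−(r + 0.03) × 4.25)], with r = 0.05 on placebo and 0.05 × HR on aspirin. HR = 0.893 with 3,255 events.

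Reducing the cumulative incidence in step 2 by the overall drop-out gives 3,013 to 3,035 events and HR 0.889. Freedman's formula agrees to within 0.001. Using 4.7 or 5 years, or one-sided alpha, keeps every result between 0.889 and 0.914. Power at HR 0.799 exceeds 99.9% in all of these variants.

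**Comparison within Appendix 2.** The dementia rate is 0.50 × 6 + 0.30 × 11 + 0.15 × 20 + 0.05 × 37 = 11.15 per 1,000, before the doubling for African American participants. Over 4.25 years, 0.799 would correspond to a depression rate of only about 1.15 to 1.25% per year, close to the dementia rate and far from 5%.

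**Where 0.799 may come from.** If 5% is used as the probability over the whole study and 3% per year is then removed: 19,000 × 0.05 × 0.97^4.25 = 834.6 events, and exp(−√(42.03/834.6)) = 0.799.

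**If participants above the threshold at baseline are left out.** Keeping 85 to 90% of participants gives a detectable hazard ratio of 0.884 to 0.895. The choice of risk set therefore does not explain 0.799 either.

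**The case against.** The strongest reply is that little depends on this figure. Depression is one of eight secondary endpoints, the 19,000 is set by the primary endpoint, and the error makes the trial look weaker than it is. No alpha, analysis or stopping decision rests on 0.799. A completed trial's null result would be read from its estimate and confidence interval, not from a planned detectable effect. All of this stands, and it limits the weight of the point. It does not make the figure right. The paragraph itself calls 5% conservative, and a higher rate would move the detectable hazard ratio still closer to 1.

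A reader might go further and infer that the endpoint rule counts people already depressed at entry, and that this dilutes the treatment effect by a calculable amount. The documents do not support that. Appendix 1, section 2.7 is silent on the baseline score; it does not say that such participants count. Sections 1.2.6, 7.1.1(d) and 7.1.3(c), Appendix 1 section 3.1(a) and Appendix 2 item 7 all speak of new or new-onset depression. The prevalence of 10 to 15% in section 1.2.6 is for depressive disorders in the elderly generally, not for scores of 8 or more in this screened cohort, and no recurrence rate is given. Section 1.2.6 also allows that aspirin might treat depression, so dilution toward 1 is not certain.

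What remains is a gap in wording. Depression is not an exclusion in section 6.2, and Appendix 1 section 3.1(a) foresees participants at or above the threshold at baseline, yet section 2.7 carries no baseline condition.

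**Conclusion.** The stated detectable hazard ratio of 0.799 is wrong for the inputs given. Those inputs yield about 3,255 to 3,837 events and a detectable hazard ratio of about 0.89 to 0.90. The spread comes only from how the 3% drop-out is combined with the 4.25 years. The result assumes proportional hazards and a constant 5% annual rate, as the paragraph does.

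Entry of the annual 5% as an overall probability fits the printed value, but this is an inference; the protocol does not say how the figure was obtained.

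The consequence is modest: understated power for a secondary endpoint, with no effect on sample size. The missing baseline condition in section 2.7 is a minor inconsistency with the new-onset wording elsewhere. No size of bias from prevalent cases is claimed.

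**What to change.** In Appendix 2, item 7, replace 0.799 with the recomputed value: about 0.90 if 4.25 years is already net of losses, or about 0.89 if 3% per year is taken off in addition. State which of the two applies.

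In Appendix 1, section 2.7, add a phrase that ties the endpoint to new-onset depression and says how participants with a baseline CES-D-10 of 8 or more are handled. Restricting the risk set is one option; keeping everyone with baseline adjustment or stratification is another. If the risk set is limited to 85 to 90% of participants (an assumed range), the figure to quote is about 0.88 to 0.90.

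The cost is one number and one or two sentences. Sample size, alpha and the Cox analysis stay as they are. Restricting the risk set would give up the participants above the threshold at entry.
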